# Adverse events

## Definition

An AE is any untoward medical occurrence in a subject or clinical investigation subject that does not necessarily have a causal relationship with any treatment. An adverse event may consist of any medical change (illness, condition, sign or symptom) in a subject after exposure to the study drug and includes:

- an event not seen prior to study drug administration
- an exacerbation of a pre-existing illness, condition, sign or symptom (e.g. increase in asthma attacks)
- a recurrence of an intermittent illness, condition, sign or symptom (e.g. migraine)
- an illness or condition diagnosed after study drug administration even though it may have been present prior to administration (e.g. cancer)

An adverse event does not include:

- a continuous persistent illness, condition, sign or symptom present before study drug administration which does not unexpectedly progress or change in severity following study drug administration
- the disease being studied or signs or symptoms associated with the disease (e.g., pain and swelling due to osteoarthritis of the knee)

## Complications of Ultrasound Guided Peripheral Nerve Blocks

Nerve block: Overall, the complication rate of ultrasound guided peripheral nerve blocks is low. The main complication is intraneuronal puncture, which leads in the minority of cases to prolonged paraesthesia or nerve damage (incidence unknown). Due to the fact that ultrasound is used for single peripheral nerve blockade, intraneuronal (intraepineural) needle tip position and subsequent administration of LA (intraepineurally) can be excluded. Haematoma formation is another possible complication, but the nerve will be blocked at areas (see above) without adjacent vessels. Infection is also a possible complication, but sterile conditions are used for the procedures.

Local anaesthetic: Ropivacaine is used as LA, which shows the lowest potency of systemic side effects. Due to the low dose of ropivacaine used in the present study (3x7.5mg in 3ml = 22.5mg = 0.75%) any systemic side effects (bradycardia, hypotension, central neurotoxic effects such as convulsion, etc.) can be excluded. Nevertheless, the volunteers are haemodynamically monitored throughout the study period for possible emergency intervention.

## Documentation and Reporting of Adverse Events

AEs will be documented throughout the entire study. In addition, SAEs which are reported to the investigator within 30 days after study termination have also to be documented using the SAE reporting form.

## Serious adverse events (SAEs)

A serious adverse event is an adverse event that:

- results in death, or
- is life-threatening (the subject was at risk of death at the time of the event)
- requires in-patient hospitalisation or prolongation of existing hospitalisation
- results is persistent or significant disability / incapacity, or
- is a congenital anomaly / birth defect, or
- is another medically important condition that may be considered a SAE when, based upon appropriate medical judgment, it may jeopardize the subject or may require intervention to prevent one of the outcomes listed above

## Causality Assessment between Adverse Events and study medication

A causality assessment between adverse events and study medication will be performed as follows:

**Not related -** clearly unrelated to the use of the test product; an evident alternative cause must be available.

**Possible -** causal relationship to the test product appears unlikely, but cannot be ruled out with reasonable certainty.

**Probable -** felt to be causally related to the test product with a high degree of likelihood.

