HR Heart rate
IMP Investigational medicinal product
IP In-plane needle guidance technique
IRB-IEC Institutional Review Board – Independent Ethics Committee
i.v. Intravenous
JPEG Joint Photography Expert Group
NSAID Non-Steroidal-Anti-Inflammatory-Drug
OTC Over the counter
PD Pharmacodynamic
PK Pharmacokinetic
PTT Partial thromboplastin time
RBC Red blood count
SUSAR Suspected Unexpected Serious Adverse Reaction
t_1/2_ Termination elimination half-time
t_max_ Time to maximum concentration
WBC White blood count

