## Serious adverse events

A serious adverse event is an AE that:

- results in death, or
- is life-threatening (the subject was at risk of death at the time of the event)
- requires in-patient hospitalisation or prolongation of existing hospitalisation
- results in persistent or significant disability / incapacity, or
- is a congenital anomaly / birth defect, or
- is another medically important condition that may be considered a SAE when, based upon appropriate medical judgment, it may jeopardize the subject or may require intervention to prevent one of the outcomes listed above

A causality assessment between adverse events and study medication will be performed as follows:

*Not related* - clearly unrelated to the use of the test product; an evident alternative cause must be available.

*Possible* - causal relationship to the test product appears unlikely, but cannot be ruled out with reasonable certainty.

*Probable* - felt to be causally related to the test product with a high degree of likelihood.

The severity of AEs will be graded according to the following scale:

*Mild* - the adverse event does not interfere in a significant manner with the subject’s normal functioning.

*Moderate* - the adverse event produces some impairment of functioning but is not hazardous to health.

*Severe* - the adverse event produces significant impairment of functioning or incapacitation and is a definite hazard to the subject’s health.

The sponsor has to inform the involved regulatory authorities and the investigator has to inform the involved ethics committee about each serious or unexpected AE/adverse drug reaction (SUSAR, that is an experience not previously reported - in nature, severity or incidence - in the current Summary of Product Characteristics that in the opinion of the investigator or sponsor might jeopardize the safety of the subjects or the further conduct of the study). SUSARs not fatal or not life threatening will be reported to the IRB-IEC and the competent regulatory authorities within 15 calendar days. SUSARs that lead to death or are life threatening will be reported within 7 calendar days.

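### Safety rules: causality is rated against the drug only, the Possible category is worded as unlikely, and the SUSAR wording contradicts the glossary

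*Protocol*

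**What the plan says.** **What is rated.** The Protocol section on causality assessment opens with "A causality assessment between adverse events and study medication will be performed as follows". The scale has three levels, each worded against the test product:

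- The lowest level, *Not related*, is reserved for events that are "clearly unrelated to the use of the test product; an evident alternative cause must be available".
- The middle level, *Possible*, applies when the "causal relationship to the test product appears unlikely, but cannot be ruled out with reasonable certainty".
- The top level, *Probable*, applies to an event "felt to be causally related to the test product with a high degree of likelihood".

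The Ethical Section repeats the scale under Serious adverse events.

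**Which harms are expected.** The section on complications of ultrasound guided blocks treats the block and the local anaesthetic separately. For the block it says: "The main complication is intraneuronal puncture, which leads in the minority of cases to prolonged paraesthesia or nerve damage (incidence unknown"). It adds "Haematoma formation is another possible complication" and also names infection. For ropivacaine at this dose it regards systemic side effects as excluded.

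**What is reported.** Under Serious adverse events, the Ethical Section requires authorities and ethics committee to be informed "about each serious or unexpected AE/adverse drug reaction (SUSAR, that is an experience not previously reported" in the product information. The same parenthesis adds that the investigator or sponsor must think the event could endanger participants or the continuation of the study. SUSARs are then due within 7 calendar days if fatal or life-threatening, and otherwise within 15. The section on information of the regulatory authorities has the same sentence without the SUSAR label and without time limits. The glossary reads "SUSAR Suspected Unexpected Serious Adverse Reaction". The section on removal of subjects sends serious adverse events to the authorities within statutory time limits, with no condition on cause or opinion.

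**The concern.** Participants are healthy volunteers with no direct health benefit, so the protocol should be able to record which harms the study caused. The study exposes them to a drug, a nerve block needle, a venous cannula and repeated blood draws, yet the only causality scale covers the drug. A tabulation by relatedness could then show a harm caused by the needle as unrelated.

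Separately, two careful assessors could place the same plausible but unproven event in different categories, because neither *Possible* nor *Probable* describes it.

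Separately again, the expedited time limits attach to a term that the protocol defines in two incompatible ways. Staff who must decide whether a 7-day or 15-day clock has started cannot settle the question from the text.

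**Working it through.** No sample size, rate or test enters here, so the check sets the passages side by side.

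**1. Applying the causality scale to the complications the protocol names.** *Not related* needs two things: the event is clearly unrelated to use of the product, and another cause is evident.

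| Event | Clearly unrelated to the drug? | Evident other cause? | Likely code |
|---|---|---|---|
| Clear needle haematoma | Yes | Yes, the needle | *Not related* |
| Puncture-site infection | Yes | Yes, the puncture | *Not related* |
| Nerve symptoms after the block | Usually not, since drug was placed at the nerve | Perhaps, the needle | Usually *Possible* |

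The first two codes answer the question the scale asks, which concerns the drug. The gap is that no second question is asked about the procedure. Haematoma or infection at the antecubital cannula (Study day) or from the seven blood samples (Pharmacokinetic Analysis) falls outside the scale in the same way.

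**2. Reading the scale from bottom to top.** *Not related* is clear absence of a relation. *Possible* is an unlikely relation that cannot be excluded. *Probable* is a highly likely one. A relation that is plausible, neither unlikely nor highly likely, matches neither of the upper two definitions.

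**3. Comparing the reporting definitions.** The protocol supports at least three readings of which events count as SUSARs:

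- A, glossary: suspected, unexpected and serious together.
- B, main clause in the Ethical Section: serious or unexpected, whether an event or a reaction.
- C, the same sentence with its parenthesis limiting the whole clause: also not previously reported, and judged able to endanger participants or the study.

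| Event | A | B | C |
|---|---|---|---|
| Unexpected, suspected, not serious | No | Yes | Only if judged to endanger |
| Serious, unexpected, suspected, not judged to endanger | Yes | Yes | No |
| Serious, suspected, already in the product information | No | Yes | No |
| Serious, unexpected, not suspected | No | Yes | Only if judged to endanger |

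None of these four event types gets the same unconditional answer from all three readings. The section on removal of subjects would send the last three to the authorities as serious events, but it refers to statutory limits and does not say whether the 7-day and 15-day limits apply.

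**4. Looking for a link between points 1 and 3.** The two reporting sections and the section on removal of subjects name no level of the causality scale as a condition for reporting. The defects are therefore separate.

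**The case against.** The strongest reply has five parts.

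- **The scale answers its own question correctly.** A haematoma from the needle is unrelated to ropivacaine. This stands, but it explains why a second rating is needed and does not remove the need.
- **Procedural harms are still captured.** The adverse event definition does not depend on cause, events are documented throughout, and the final contact asks about ulnar nerve function and the puncture site. The protocol also argues that ultrasound guidance, the absence of adjacent vessels and sterile conditions make these complications unlikely. All of this stands. What is lost is attribution, not capture.
- **Possible errs on the safe side.** Anything that cannot be ruled out is at least *Possible*, so a suspected reaction is not lost. This stands. The remaining problem is inconsistent coding and a label that contradicts its definition.
- **The SUSAR parenthesis may explain only the word unexpected, and the glossary may govern the clocks.** That is a fair reading. It is not the only one, and the sentence attaches the label directly to serious or unexpected events.
- **The adverse event form is not shown and may record more.** That is possible, since the Documentation section refers the judgement to that page. The written rule would still mention the drug only.

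A reader might infer more than the documents support. One inference is that a needle-related nerve injury has to be coded *Not related*. It does not, because the event must also be clearly unrelated to the product, and nerve symptoms after ropivacaine placed at the nerve rarely are. *Use of the product* can even be read to include its injection. Another inference is that a *Not related* code would block expedited reporting. No section makes reporting depend on that code.

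**Conclusion.** Three separate defects in the stated safety rules hold:

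1. Of the three procedural complications named, two (haematoma and infection), when unambiguous, would be recorded as unrelated although the study caused them.
2. A plausible but unproven relation has no fitting category.
3. The SUSAR wording in the Ethical Section contradicts the glossary, so the events that start the 7-day and 15-day clocks are not determined.

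The size is modest. The number of events affected cannot be estimated: the protocol gives the incidence of nerve damage as unknown and offers no rate for haematoma or infection. No loss of a serious event report is shown, since serious events go to the authorities whatever their cause. Nor is an understated published count shown, because the statistical sections plan no analysis by relatedness. The primary analysis and the sample size are unaffected. The first point assumes that assessors read *test product* as the drug and not as the act of injecting it.

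**What to change.** - **Causality, in both places where the scale appears.** Rate each adverse event twice: against ropivacaine, and against the study procedures (block, cannula, blood draws). Count it as study-related if either rating is at least *Possible*.
- **Possible.** Reword it as a reasonable possibility that is not proven. Say explicitly that events which cannot be confidently excluded stay in this category, so that no new gap opens just above *Not related*.
- **Reporting.** Reconcile the section on information of the regulatory authorities and the Ethical Section with the glossary meaning of SUSAR and with the rule for serious events in the section on removal of subjects. State what happens to serious events that are not SUSARs. Keep the existing 7-day and 15-day limits.

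The cost is one extra item on the adverse event form and a wording amendment. The downside is that slightly more events will be counted as study-related. Dose, sample size and analysis do not change.

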## Severity of the adverse event

The severity of AEs will be graded according to the following scale:

**Mild** - the adverse event does not interfere in a significant manner with the subject’s normal functioning.

**Moderate -** the adverse event produces some impairment of functioning but is not hazardous to health.

**Severe -** the adverse event produces significant impairment of functioning or incapacitation and is a definite hazard to the subject’s health.

## Information of the regulatory authorities and the IRB-IEC

The sponsor has to inform the involved regulatory authorities and the investigator has to inform the involved ethics committee about each serious or unexpected AE/adverse drug reaction (that is an experience not previously reported - in nature, severity or incidence - in the current Summary of Product Characteristics that in the opinion of the investigator or sponsor might jeopardize the safety of the subjects or the further conduct of the study).

# Premature termination of the trial

The trial will be terminated prematurely in any of the following cases for example:

- If adverse events occur which are so serious that the resulting risk-benefit ratio becomes unacceptable
- If the number of drop-outs is so large that proper conclusion of the trial is no longer a realistic possibility
- If the results of parallel clinical trials reveal unacceptable risks
- If results of any interim analyses and the status of drug development should change, such that the trial would no longer be a necessary part of the clinical program
- Attempted or proven fraud
- Slow recruitment
- Poor quality of data
- Non-compliance with protocol.

# REMOVAL OF SUBJECT FROM TRIAL

Any subject who discontinues participation to the trial within two hours after onset of drug administration, is defined as ”drop-out”. Although subjects are not obliged to give reason(s) for withdrawal, the investigator should make a reasonable effort to ascertain the reason(s), while fully respecting the subject’s rights.

The Investigator may remove the subject from the trial for any of the following reasons:

- Failure to observe the trial conditions or instructions from the trial team
- Failure to comply with any aspect of the protocol
- Occurrence of AEs
- Recurrent diseases which the investigator deems to be unacceptable
- Detection of drugs or addictive substances

For follow-up procedures of AEs the subjects will stay under medical supervision (in hospital or via telephone contact) unless the physician believes that all adverse events have resolved or a final assessment can be made. Appropriate control measurements may be initiated for safety parameters. All AEs will be documented and assessed by physicians. Serious adverse events will be communicated to the responsible authorities within the legal timelines.

If a subject is removed or discontinues, a replacement subject will be enrolled who will follow the same procedure as described for the original subject. The reason(s) for drop-out must be recorded.

# STATISTICAL / ANALYSIS SECTION

## Sample size calculation

A previous study with ropivacaine 0.75% for ulnar nerve blockade showed a duration of sensory blockade of 350 min with the largest SD of 54 minutes.^2^ Assuming a nominal difference in means between the study groups of 35 minutes, a pooled standard deviation of 54 minutes, the study would require a sample size of 39 for each group (i.e. a total sample size of 78, assuming equal group sizes), to achieve a power of 80% and a level of significance of 5%. To enable nonparametric analysis, the sample size is increased by 15% to 90 subjects. For a larger nominal 15% difference, the total sample size is reduced to 42 subjects.

## Interim-Analysis

After 2 x 12 cases, we perform an interim analysis for re-evaluation of the initially calculated number of 90 cases (power = 80%, level of significance = 5%). Based on the results of the primary outcome parameter after interim-analysis, a power analysis (to achieve a power of 80% and a level of significance of 5%) to find a nominal difference of 10 to 15% will be performed to determine the number of additional study cases which will be investigated.

## Randomization

-

## PD, PK and morphometric data analysis

Pharmacodynamic data analysis: The primary outcome is duration of sensory block. Secondary outcomes include onset of sensory block, onset and duration of motor block. Data will be presented as mean (SD), median [interquartiles] and count (%) and analysed using unpaired two-sided Student *t-*, Mann-Whitney *U-*, log-rank and Fisher exact statistics. Mixed effects linear models will be used to adjust for subject characteristics. Data will be analysed using Stata 17.0 and NCSS 2020.

Pharmacokinetic data analysis: Secondary outcomes, including parameters such as C_max_, t_max_and AUC will be estimated and analysed using statistics as listed above.

Morphometric data analysis: Differences between grey scales of nerves and nerve visibility (differences between nerves and surrounding tissue) and differences in the Vienna Scoring System will be compared using unpaired two-sided Student *t-* or Mann-Whitney *U-* statistics as appropriate. Mixed effects linear models will be performed to determine the correlation of nerve visibility with morphometric variables.

# ETHICAL SECTION

## Safety precautions

During the period of study visits subjects will be observed by a physician or an experienced nurse.

## Inconveniences and risks for subjects

Side effects of *ropivacaine* (as enlisted in detail in the Summary of Product Characteristics, Appendix 1) include local numbness, dizziness, hypotension, nausea, vomiting, respectively.

## Risk/benefit assessment

Overall, the risks associated with the study are low.

### Individual benefit

Subjects do not have direct a health benefit from participation. The benefit is attributed to overall benefits for patients and scientific community.

## Adverse events

An AE is any untoward medical occurrence in a subject or clinical investigation subject that does not necessarily have a causal relationship with any treatment. An adverse event may consist of any medical change (illness, condition, sign or symptom) in a subject after exposure to the study drug and includes:

- an event not seen prior to study drug administration
- an exacerbation of a pre-existing illness, condition, sign or symptom (e.g. increase in asthma attacks)
- a recurrence of an intermittent illness, condition, sign or symptom (e.g. migraine)
- an illness or condition diagnosed after study drug administration even though it may have been present prior to administration (e.g. cancer)

An adverse event does not include:

- a continuous persistent illness, condition, sign or symptom present before study drug administration which does not unexpectedly progress or change in severity following study drug administration
- the disease being studied or signs or symptoms associated with the disease (e.g., pain and swelling due to osteoarthritis of the knee)

AEs will be documented throughout the entire study. In addition, SAEs which are reported to the investigator within 30 days after study termination have also to be documented using the SAE reporting form.

## Serious adverse events

A serious adverse event is an AE that:

- results in death, or
- is life-threatening (the subject was at risk of death at the time of the event)
- requires in-patient hospitalisation or prolongation of existing hospitalisation
- results in persistent or significant disability / incapacity, or
- is a congenital anomaly / birth defect, or
- is another medically important condition that may be considered a SAE when, based upon appropriate medical judgment, it may jeopardize the subject or may require intervention to prevent one of the outcomes listed above

A causality assessment between adverse events and study medication will be performed as follows:

*Not related* - clearly unrelated to the use of the test product; an evident alternative cause must be available.

*Possible* - causal relationship to the test product appears unlikely, but cannot be ruled out with reasonable certainty.

*Probable* - felt to be causally related to the test product with a high degree of likelihood.

The severity of AEs will be graded according to the following scale:

*Mild* - the adverse event does not interfere in a significant manner with the subject’s normal functioning.

*Moderate* - the adverse event produces some impairment of functioning but is not hazardous to health.

*Severe* - the adverse event produces significant impairment of functioning or incapacitation and is a definite hazard to the subject’s health.

The sponsor has to inform the involved regulatory authorities and the investigator has to inform the involved ethics committee about each serious or unexpected AE/adverse drug reaction (SUSAR, that is an experience not previously reported - in nature, severity or incidence - in the current Summary of Product Characteristics that in the opinion of the investigator or sponsor might jeopardize the safety of the subjects or the further conduct of the study). SUSARs not fatal or not life threatening will be reported to the IRB-IEC and the competent regulatory authorities within 15 calendar days. SUSARs that lead to death or are life threatening will be reported within 7 calendar days.

